### Data collection

2.5

The study data collection process is outlined in Table 1.

**Table 1 T1:**
[figure not shown]
Treatment schedule and outcome measures.

### Primary outcomes

2.6

The National Institutes of Health's Symptom Score Index (NIH-CPSI) score for CP/CPPS will be used as the primary outcome measure. Every dimensions (degree of pain, urinary symptoms, quality of life) of NIH-CPSI will be evaluated, and the lower the total score, the lighter the clinical symptoms of the patient.

### Secondary outcomes

2.7

The second outcome measure is based on TCM syndrome evaluation criteria.(1) Healing: The clinical symptoms and signs of TCM disappear or almost disappear, and the syndrome score is reduced by ≥90%; (2) Significant effect: The clinical symptoms and signs of TCM are obviously improved, and the syndrome score is reduced by ≥60%; (3) Effective: Chinese medicine Clinical symptoms and signs have improved, syndrome scores decreased by < 60%, but ≥30%; (4) Invalid: The clinical symptoms and signs of TCM were not improved, even worse, and the syndrome score was reduced by < 30%. Integral variation formula (Nimodipine method: [(pre-treatment score - post-treatment score) ÷ pre-treatment score] × 100%.

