### Setting and participants

2.2

This study will be conducted in China. Patients will be recruited from Urology/Andrology departments of Dongzhimen Hospital. We will enroll participants based on the following inclusion criteria:

1.Those who meet the CP / CPPS western medical diagnostic criteria;2.Those whose disease course exceeds 3 months;3.Twenty years old ≤ age ≤ 50 years old;4.Patients who have been treated before the consultation can be included in the study after at least 2 weeks of drug withdrawal;5.Those who have signed informed consent.

Participants who meet the following exclusion criteria will not be enrolled:

1.Patient with a history of pelvic surgery;2.Persons with abnormal development or infection of urogenital system;3.Prostate tuberculosis, benign prostatic hyperplasia and prostate cancer, acute urethral syndrome;4.Patients with severe physical illness, systemic failure, and allergies to tamsulosin hydrochloride sustained-release capsule drugs;

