#### Sample size

2.8.1

Based on the results of our previous study, the effective rate of CP/CPPS in the intervention group was P1 = 0.80. The PSD effective rate of the control group was P2 = 0.65 [(two-sided type I error rate of 0.05, α = 0.05); (one-sided type I error rate of 0.10, β = 0.10)]. Substituting f (α, β) into the formula is as follows: n1 = n2 = 10.5 × (0.8 × 0.2 + 0.65 × 0.35) ÷ 0.152 = 75. The lost follow-up rate of patients will be controlled at 10%, so an additional 8 cases are added to each group. n1 = n2 = 83, that is, 83 cases will be taken from each of the intervention group and the control group. According to Cohen, this effect size is considered “moderate”.

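### Banding the TCM syndrome score by percentage change and comparing the bands by chi-square wastes information; analyse the score in points, adjusted for baseline

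*Protocol article*

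**What the plan says.** All references are to the protocol article.

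- **Section 2.7, Secondary outcomes.** The TCM syndrome score is turned into a percentage fall, "pre-treatment score - post-treatment score) ÷ pre-treatment score] × 100" per cent, and cut into four grades: at least 90%, at least 60%, 30% to under 60%, and under 30%. The lowest improving grade, Effective, is "syndrome scores decreased by < 60%, but ≥30" per cent. The grade of no effect, Invalid, applies when "the syndrome score was reduced by < 30" per cent. Each grade also has a clinical descriptor (for example, that symptoms and signs have improved).
- **Section 2.2, Setting and participants.** Entry rests on "Those who meet the CP / CPPS western medical diagnostic criteria", on "Those whose disease course exceeds 3 months", on age 20 to 50, on consent, and on a washout rule under which treated patients "can be included in the study after at least 2 weeks of drug withdrawal". No inclusion or exclusion criterion mentions a TCM syndrome or a minimum score.
- **Section 2.8.3, Statistical analysis.** Count data are summarised as rates and composition ratios and compared by chi-square. The rank sum test is reserved for measurement data that are not normal. No test is assigned to the grades by name, but four grades per arm are count data under this wording.

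**The concern.** A score in points is measured before and after treatment and then reduced to one of four labels. Four things follow.

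1. Differences within a band are lost.
2. An ordinary chi-square test treats the four grades as unordered categories, so a consistent shift towards better grades gets no credit for its direction.
3. The number of points needed for a given grade depends on where the patient started, so the grade mixes entry severity with change.
4. The percentage has no value when the pre-treatment score is 0.

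What is at stake is the power and readability of the only outcome in section 2.7. The trial could measure a real difference in TCM symptoms and fail to show it because of how the scores are summarised and tested.

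**Working it through.** **Step 1: what the bands do (arithmetic only).**

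- Fall from 3 to 2: 1 ÷ 3 = 33%, which meets the Effective cut-off.
- Fall from 20 to 15: 5 ÷ 20 = 25%, which falls in the Invalid band.
- On a whole-number score, the smallest fall reaching 30% is 1 point from a baseline of 1 to 3, 2 points from 4 to 6, 3 points from 7 to 10, and 6 points from 20 (0.3 × 20).
- Baseline 0: the denominator is 0, so no percentage exists.

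**Step 2: cost in power (assumed example).** The article gives no range, error or baseline distribution for the score, so every input except the 75 per arm is an assumption. The 75 is the article's number per group before its dropout allowance (section 2.8.1). It is used only as a size for the example, and whether it is adequate is a separate matter.

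- Baseline: rounded normal, mean 14, SD 6, minimum 1.
- Additive effect: post = 10 + 0.5 × (baseline − 14) − 2 × arm + normal(0, 4), rounded, minimum 0.
- Proportional effect: post = baseline × fraction retained, rounded, minimum 0. The mean fraction is 0.70 (control) v 0.58 (intervention) in one case and 0.50 v 0.38 in the other, with SD 0.28.
- 3,000 simulated trials per scenario, two-sided 5% level. The Monte Carlo standard error is at most √(0.25 ÷ 3000) = 0.9 percentage points. The ranges below span repeated runs and, in the right-hand column, both proportional cases.

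| Analysis | Additive, 2 points | Proportional, two cases |
|---|---|---|
| Points, adjusted for baseline | 85–86% | 64–67% |
| Rank test on four grades | 74–76% | 64–67% |
| Chi-square on four grades | 58–60% | 45–51% |
| Chi-square, fall ≥30% v less | 65–66% | 41–57% |

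**Step 3: where the loss arises.** With an additive effect, banding alone (points to rank test) costs about 10 percentage points, and ignoring the order (rank test to chi-square) costs about 16 more. With a proportional effect, banding costs essentially nothing when the order is kept, and ignoring the order costs about 16 to 20 points. The loss from chi-square on four grades is therefore present under both models. The loss from banding alone depends on how treatment acts.

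**Step 4: chance grading at low baselines.** If the change has SD 3 points and there is no true change, the chance of a fall of at least 30% is 1 − Φ(0.3 × baseline ÷ 3): 38% at baseline 3, 31% at 5, 16% at 10 and 2% at 20. With SD 2 the figures are 33%, 23%, 7% and 0.1%. The direction is clear; the size depends wholly on the unseen scale. In the simulated population only about 8% of patients have a baseline of 5 or less, so this mechanism does not drive the power figures in step 2.

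**The case against.** The strongest reply is that proportional relief is a legitimate thing to measure, that its cut-offs are fixed in advance, and that an additive model favours the analysis in points by construction. This stands in part. Under a proportional effect, a rank test on the grades matches the adjusted analysis. It does not rescue chi-square on the four grades, which loses power under both models.

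The grades are also not defined by percentage alone, because each carries a clinical descriptor. That is correct, and it means the percentages in step 4 are chances of meeting the numerical cut-off, not of receiving the grade. It restores neither the lost points nor a value at baseline 0.

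A reader might infer three stronger things that the article does not support.

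- *Mildly affected patients will become responders by noise.* The scale, its error and the baseline distribution are not given. If typical scores are near 20, the chance figures above are 2% or less.
- *Patients with a zero baseline will be dropped from the Full Analysis Set.* Section 2.8.2 says nothing of the kind. Handling of zeros is a detail that the analysis plan may settle, and men with diagnosed disease of more than 3 months will probably seldom score 0.
- *The grading favours one arm.* Chance grading should act alike in both randomised arms. It dilutes a difference and does not create one.

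It is also tempting to link these grades to the sample size, where "the effective rate of CP/CPPS in the intervention group was P1 = 0.80" and "The PSD effective rate of the control group was P2 = 0.65". Section 2.8.1 does not define that effective rate, so the link is not established.

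**Conclusion.** The point holds as an inefficiency in a secondary outcome. Four bands compared by chi-square use the measured score poorly. In the assumed example the cost against baseline-adjusted points is about 26 percentage points of power with an additive effect (86% v 60%), and about 15 to 20 with a proportional one (about 65% v 45 to 50%). A rank test on the same grades would lose about 10 points in the first case and none in the second.

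These sizes rest on an assumed scale, baseline spread and residual variation, and on reading section 2.8.3 as sending the grades to chi-square. The dependence of the grade on entry severity and the undefined value at baseline 0 are arithmetic and need no assumption, but how often either matters in practice is unknown. The NIH-CPSI primary outcome is not touched.

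**What to change.** In section 2.7, make the secondary comparison the TCM syndrome score in points at week 4 (the end of the 4-week course), compared between arms with the pre-treatment score as covariate, and add that model to section 2.8.3. It is defined for every patient with both scores, including one who starts at 0. Keep the four grades as a supportive summary. If they are tested at all, use a test that respects their order.

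The cost is a change of wording and one regression on scores that the percentage formula already requires. The downside is that the effective rate customary in TCM reports becomes supportive. Section 4 states that recruitment had not begun at submission, so the change could then be made before any outcome data existed.

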### Statistical consideration

2.8

#### Sample size

2.8.1

Based on the results of our previous study, the effective rate of CP/CPPS in the intervention group was P1 = 0.80. The PSD effective rate of the control group was P2 = 0.65 [(two-sided type I error rate of 0.05, α = 0.05); (one-sided type I error rate of 0.10, β = 0.10)]. Substituting f (α, β) into the formula is as follows: n1 = n2 = 10.5 × (0.8 × 0.2 + 0.65 × 0.35) ÷ 0.152 = 75. The lost follow-up rate of patients will be controlled at 10%, so an additional 8 cases are added to each group. n1 = n2 = 83, that is, 83 cases will be taken from each of the intervention group and the control group. According to Cohen, this effect size is considered “moderate”.

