**Methods/design::**

This pragmatic randomized controlled trial will recruit 166 patients who are diagnosed with CP/CPPS. Simple randomization to conventional drug treatment with a 1:1 allocation ratio will be used. Ten 30-minute acupuncture sessions will be provided to patients assigned to the Intervention group. All participants will continue to receive conventional drug treatment. The selection of outcomes will be evaluated by Health's Symptom Score Index (NIH-CPSI) score at week 4.

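### The sample size rests on a binary effective rate, but the primary outcome is the NIH-CPSI score, so the planned 90% power does not apply to it; nor does it hold for the rate itself

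*Protocol article*

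**What the plan says.** Section 2.6 (Primary outcomes) states that the NIH-CPSI "score for CP/CPPS will be used as the primary outcome measure". It adds: "Every dimensions (degree of pain, urinary symptoms, quality of life) of NIH-CPSI will be evaluated". The same sentence then interprets the total score, lower being better. The Methods/design part of the abstract gives the time point: "Symptom Score Index (NIH-CPSI) score at week 4".

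Section 2.8.1 (Sample size) compares two proportions. For the intervention arm, "the effective rate of CP/CPPS in the intervention group was P1 = 0.80"; for the control arm, "The PSD effective rate of the control group was P2 = 0.65". Alpha is 0.05 two-sided and beta is 0.10. The formula is reported to give 75 per arm, and 8 per arm are added for 10% loss, making 83 per arm and 166 in total. The section calls the effect moderate according to Cohen.

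The only place where the article defines an effective category is section 2.7: "The second outcome measure is based on TCM syndrome evaluation criteria". There, graded percentage reductions in a TCM syndrome score separate the response categories, with 30% as the lowest threshold for a response.

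Section 2.8.3 (Statistical analysis) compares measurement data by t test or rank sum test, count data by chi-square test, and repeated measurements between groups by MANOVA.

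**The concern.** A power statement applies only to the endpoint and test for which it was calculated. Here the calculation concerns a difference in proportions, while the primary outcome is a score whose planned tests compare means, ranks or mean vectors. Nothing in the article connects the two: there is no rule that turns NIH-CPSI into a response, and no score difference or standard deviation.

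The basis of the rate is also unclear. Section 2.8.1 ties it to no scale. The control figure carries the label PSD, a term that is not defined and not used elsewhere in the article, so it is uncertain whether 0.65 describes CP/CPPS patients on tamsulosin.

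What is at stake is the justification for enrolling 166 men. As written, the plan does not say what NIH-CPSI difference the trial is designed to detect, so nobody can tell before recruitment whether the size suits the primary question.

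**Working it through.** **Inputs from section 2.8.1.** P1 = 0.80, P2 = 0.65, two-sided alpha 0.05, beta 0.10 (power 0.90), f(alpha, beta) = 10.5, 75 per arm, 10% loss, 83 per arm.

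**1. The plan's own figure.**
- Multiplier: (1.960 + 1.282)² = 10.51, so 10.5 is right for two-sided 5% and 90% power.
- Variance term: 0.8 × 0.2 + 0.65 × 0.35 = 0.16 + 0.2275 = 0.3875.
- Denominator: (0.80 − 0.65)² = 0.0225. The printed 0.152 is most likely 0.15² with the superscript lost.
- Result: 10.5 × 0.3875 / 0.0225 = 180.8, so **181 per arm**.
- Taking 0.152 literally gives 10.5 × 0.3875 / 0.152 = 26.8. Neither reading gives 75.
- Other standard forms at the same alpha and power do not give 75 either: 185 (pooled variance), 198 (continuity-corrected), 184 (arcsine).
- The nearest variant found is one-sided alpha 0.10 with 80% power, which gives 78. It contradicts the section's own alpha and beta.

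**2. Power for the rates at the planned size.**
- Standard error with 75 per arm: √(0.3875 / 75) = 0.0719.
- 0.15 / 0.0719 = 2.087, and 2.087 − 1.960 = 0.127, so power is about **55%**. With a pooled variance under the null it is 54%.
- If all 83 per arm are evaluable, power is 59% (58% pooled).
- The allowance for loss is not the problem: 75 / 0.9 = 83.3, close to the 83 planned.

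**3. What the planned size gives for a score.** The article supplies no NIH-CPSI difference or standard deviation, so the result can only be expressed in standard deviation units (d). For a two-sided 5% t test with 75 evaluable per arm (noncentral t):
- Detectable d: **0.53 at 90% power** and **0.46 at 80% power**.
- Normal-approximation check: (1.960 + 1.282) × √(2 / 75) = 0.529, and (1.960 + 0.842) × √(2 / 75) = 0.457.

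| Assumed true d | Power, 75 per arm |
|---|---|
| 0.3 | 45% |
| 0.4 | 68% |
| 0.5 | 86% |
| 0.6 | 95% |

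In points, the 90% figure is 0.53 times the standard deviation. As an illustration only, an assumed standard deviation of 5 to 10 points gives 2.7 to 5.3 points.

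**4. Whether the Cohen label supplies the missing link.** For two proportions Cohen's measure is h = 2·arcsin√0.80 − 2·arcsin√0.65 = 0.34. It describes the rates, and the section never converts it to a score difference.

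**The case against.** **The rate may be an NIH-CPSI responder rate.** It comes from a previous study that is not shown, and section 2.8.1 names no scale. This stands as a limit: a reader might infer that the trial was sized on the secondary TCM outcome, because that is the only effective category defined, but the article does not say so. The mismatch survives either way. If an NIH-CPSI response was meant, it is undefined, and the stated primary outcome is still the score.

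**The mismatch does not prove low power.** This also stands. At d = 0.5 the planned size has about 86% power. A completed trial could in any case be judged by its estimate and confidence interval, so it would be wrong to say that no result could be interpreted.

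**The dimensions are not four primary tests.** A reader might infer from section 2.6, with its plural heading, that the total and three dimensions are co-primary, each tested at 5%, and so that the false-positive rate is inflated. The documents do not support this. The dimensions are only to be evaluated; no co-primary status and no rule of success on any one of four is stated, and the abstract names a single score. What remains is an ambiguity about which measure decides the trial.

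**PSD may be a stray label.** That is plausible, since the intervention rate is attributed to CP/CPPS. It calls for verification and carries no further weight.

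**Detail may sit in a fuller document.** A fuller document could add an NIH-CPSI calculation. It would not make the published one apply to a score, nor correct its arithmetic.

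**Conclusion.** The point holds. The planned 90% power belongs to a comparison of proportions and does not apply to the NIH-CPSI score at week 4. It fails for the proportions as well: the plan's own inputs require 181 per arm, and the planned 75 evaluable per arm give about 55% power. The stated power is therefore valid for neither endpoint.

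The mismatch and the arithmetic rest on the article's text alone. The detectable differences of 0.53 and 0.46 assume a two-sided 5% t test with 75 evaluable per arm; any figure in points also needs a standard deviation that the article does not give. Whether the trial is adequately sized for NIH-CPSI cannot be settled from the document. This should be corrected before recruitment, which had not begun when the article was submitted.

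**What to change.** 1. In section 2.6, name the NIH-CPSI total score at week 4 as the single primary endpoint and the pain, urinary and quality-of-life dimensions as supporting measures.
2. In section 2.8.1, replace the proportion calculation with the detectable NIH-CPSI difference at the planned size: d about 0.53 at 90% power and 0.46 at 80%, for 75 evaluable per arm and a two-sided 5% t test. Convert it to points with the standard deviation from the sponsor's previous study, if available, and say whether a difference of that size is worth detecting.
3. If the effective-rate calculation is kept, label it secondary, define the rate and its scale, verify the control figure now labelled PSD, and state its power as about 55%.

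**Cost.** Two sections are rewritten, and the stated power becomes less favourable. Restating the design at 166 adds no patients in itself. If the detectable difference proves too large to be useful, the size has to be reconsidered. By the normal approximation, 90% power needs 85 evaluable per arm at d = 0.5 (85 / 0.9, so 95 randomised) and 132 at d = 0.4 (132 / 0.9, so 147 randomised), against 83 planned.

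### The sample-size formula gives 181 per arm, not 75, so the planned 166 patients give about 54–59% power for 80% vs 65%, not the 90% implied by β = 0.10

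*Protocol article*

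**What the plan says.** Section 2.8.1 (Sample size) of the protocol article prints every input to the calculation:

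- Intervention rate: "the effective rate of CP/CPPS in the intervention group was P1 = 0.80".
- Control rate: "The PSD effective rate of the control group was P2 = 0.65".
- Error rates: "two-sided type I error rate of 0.05, α = 0.05" and "one-sided type I error rate of 0.10, β = 0.10".
- Calculation: "n1 = n2 = 10.5 × (0.8 × 0.2 + 0.65 × 0.35) ÷ 0.152 = 75".
- Losses: "The lost follow-up rate of patients will be controlled at 10%, so an additional 8 cases are added to each group", which brings each group to 83.

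The section ends by describing the effect size: "According to Cohen, this effect size is considered" moderate. The Abstract (Methods/design) carries the total forward: "This pragmatic randomized controlled trial will recruit 166 patients who are diagnosed with CP/CPPS". The article gives no other justification for 166.

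**The concern.** The printed inputs and the printed result do not belong together. The multiplier 10.5 is right for two-sided 5% and 90% power, and a 15-point difference between rates of this size needs far more than 75 per arm at those error rates. Because 75 leads directly to 83 per arm and 166 in total, the error sets the size of the trial.

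At stake is how a result on this contrast would be read. A reader who accepts section 2.8.1 would take a non-significant difference in effective rates as coming from a comparison with a 10% chance of missing a true 15-point benefit. With the planned numbers, that chance is above 40%.

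Two smaller faults sit in the same section. β = 0.10 is labelled a one-sided type I error rate when it is the type II error rate, and the effect is called moderate without saying on which index.

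**Working it through.** **Inputs (section 2.8.1).** P1 = 0.80, P2 = 0.65, α = 0.05 two-sided, β = 0.10, f(α, β) = 10.5, 1:1 allocation, 10% loss.

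**Multiplier.** (1.960 + 1.2816)² = 10.51. The article's 10.5 is correct and confirms that 90% power was intended.

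**The article's own formula.** n = f × [P1(1 − P1) + P2(1 − P2)] ÷ (P1 − P2)².

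- Variance term: 0.16 + 0.2275 = 0.3875.
- Numerator: 10.5 × 0.3875 = 4.069.
- Denominator 0.15² = 0.0225: 4.069 ÷ 0.0225 = 180.8, so **181 per arm**.
- Denominator literally 0.152: 4.069 ÷ 0.152 = 26.8.

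The stated 75 is not reproduced by either reading.

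**Could another standard method give 75?** Per-arm sizes for 80% vs 65% at α = 0.05:

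| Setting | Unpooled or pooled | With continuity correction |
|---|---|---|
| One-sided, 80% power | 107–109 | 122 |
| One-sided, 90% power | 148–150 | 163 |
| Two-sided, 80% power | 136–138 | 151 |
| Two-sided, 90% power | 181–185 | 198 |

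The arcsine method at two-sided 90% gives 184. Half of 180.8 is 90.4, so confusing total with per-arm size does not explain it either. Solving backwards, n = 75 needs f = 75 × 0.0225 ÷ 0.3875 = 4.35, not 10.5.

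**Power at the planned size** (80% vs 65%, two-sided 5%). Unpooled formula: power = Φ(0.15 ÷ √(0.3875 ÷ n) − 1.960).

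- n = 75: 0.15 ÷ √(0.3875 ÷ 75) = 2.087; Φ(0.127) = 0.550.
- n = 83: 0.15 ÷ √(0.3875 ÷ 83) = 2.195; Φ(0.235) = 0.593.

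| Evaluable per arm | Unpooled | Pooled | Exact power of chi-square test |
|---|---|---|---|
| 75 | 55.0% | 53.9% | 54.0% |
| 83 | 59.3% | 58.2% | 58.6% |
| 181 | 90.0% | 89.5% | 89.7% |

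Chi-square is the test that section 2.8.3 names for count data. Even a one-sided test would give only 66% (n = 75) to 70% (n = 83).

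**Size needed after losses.** 181 ÷ 0.90 = 201.1, so 202 per arm and 404 in total. The additive step the article uses (75 × 1.1 = 82.5, so 83) would give 181 × 1.1 = 199.1, so 200 per arm and 400 in total. Either is about 2.4 times 166.

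**Difference detectable with 90% power against a 65% control rate.** With 75 per arm, an intervention rate of about 87% (22 points); with all 83, about 86% (21 points).

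**Size of the effect.** Cohen's h = 2 arcsin√0.80 − 2 arcsin√0.65 = 0.34. On the conventional benchmarks for h of 0.2 (small) and 0.5 (medium), which the article does not give and are assumed here, this lies between the two.

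**The case against.** The arithmetic is not in dispute, but several limits deserve a fair hearing.

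- **The contrast is not the primary outcome.** Section 2.6 makes the NIH-CPSI score primary, and response categories appear only under the secondary TCM outcome in section 2.7. No mean difference or standard deviation is given, so power for the primary comparison is unknown and could be higher or lower. This stands: the 54–59% applies to the effective-rate contrast only. It does not rescue the calculation, which is the sole justification for 166.
- **The article never writes 90%.** True. It is implied by β = 0.10 and confirmed by the multiplier 10.5.
- **The superscript may have been lost in text extraction.** Probably so, and it is not counted as an error here. Neither reading gives 75.
- **An input, not the result, may be wrong.** With P2 = 0.56 the same formula gives 10.5 × (0.16 + 0.2464) ÷ 0.24² = 74.1, which rounds up to 75. The previous study is not shown, so this cannot be excluded. But the article uses 0.65, and 0.35 with it, consistently, so as written the inputs and result still conflict.
- **The Cohen remark is a labelling matter.** It is. The article names no index, and no design decision depends on it. It is secondary.

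**Conclusion.** The concern holds. On the inputs in section 2.8.1, the formula gives 181 evaluable per arm; the article prints 75, less than half of that. For 80% vs 65% at two-sided 5%, the type II error at the planned size is about 41–46%, against the stated 10%.

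This rests on reading 0.152 as 0.15 squared, on taking 90% power from β = 0.10 and f = 10.5, and on the stated rates being those intended. It says nothing about power for the NIH-CPSI score. It must be corrected because the false figure is the only basis given for the recruitment target.

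**What to change.** In section 2.8.1:

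1. Check P1 and P2 against the previous study and reconcile them with the result. If 0.80 and 0.65 stand, show that the formula gives 181 and remove 75 as its result.
2. If 166 stays, state the power it gives for 80% vs 65%: 54–55% with 75 evaluable per arm, 58–59% with all 83. State the difference detectable with 90% power: 65% to about 87% with 75 per arm, or to about 86% with 83. Justify 166 on the primary NIH-CPSI outcome.
3. Relabel β = 0.10 as the type II error rate.
4. Delete the statement that the effect is moderate, or correct it by naming the index and its value (h = 0.34).

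The cost is a change of wording and numbers. Section 4 (Trial status) says recruitment had not begun when the manuscript was submitted; whether that is still so is not known. The correction needs no additional patients, but the reported power becomes less favourable. Restoring 90% power for 80% vs 65% would be a separate decision and would raise enrolment to about 404.
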